**Comparison of brushing techniques- a multidisciplinary, randomised study teaching oral hygiene skills**

**Trial Protocol**

**(Translation of the original German protocol plus list of amendments)**

**Aim of the Study**

The aim of the study is a longitudinal controlled comparison of effectiveness of different brushing techniques. Three of the best known brushing techniques (Stillman, Fones and modified Bass) should be compared with each other and a control group. When planning such a study one has to take into account, that you need more than only dental experts to teach a brushing technique. Furthermore it is necessary to implement knowledge of movement sciences such as best teaching of fine motor motion sequence. In addition it requires psychological expertise to teach information in a way that it can be optimal processed, remembered and transformed and motivational aspects to support the application in everyday life. The present study will follow this approach to connect these three disciplines. A PowerPoint presentation will be worked out for every technique (Stillman, Fones and Bass) taking into account in all presentations knowledge of dentistry, movement sciences and psychology. The presentations are constructed in a way that participants are able to get through the presentation by themselves and to follow them in his/her own tempo. Additionally, they are able to follow single training steps in a mirror placed nearby. Another aim of this study is to evaluate the success of teaching these techniques with the help of clinical parameters in the following period. An equal focus is placed on oral hygiene skills, actual oral hygiene and oral health of the participants.

**State of research**

Oral hygiene at home has a special role in prevention of plaque associated diseases, like for example gingivitis, periodontitis and tooth decay. Especially gingivitis and periodontitis receive particular significance, because their prevalence constantly increases in the last years (Micheelis et al., 2008). Latest representative survey shows that more than 90 % of adults and seniors have gingivitis. The prevalence of periodontitis differed between 30-70% depending on method of collecting data, analysed severity code und age group that was examined. This is quite surprising taking into account that daily plaque removal is deemed to be an effective method of prevention. At the same time 60 % of seniors and over 70% of adults state to practise oral hygiene twice a day (Micheelis & Schiffner, 2006). Current data of our working group show that the percentage of people who practice at least once a day oral hygiene is even higher (Deinzer et al., in press). If at least 70 % stated to practice daily oral hygiene and the same time the prevalence of disease associated with plaque is 90 % this indicates a lack of oral hygiene skills. The data available suggest that patients have not the necessary skills to remove all dental plaque deposits with their oral hygiene at home. Studies of our working group point into this direction, too. Students are not able to remove more than 60 % of marginal plaque deposits on average (Granrath, 2007). Even less favourable data have been found for patients who participate in a study of oral hygiene skills teaching in prophylaxis-oriented dental practices (Deinzer et al., in preparation).

The increasing prevalence of periodontal diseases despite of high brushing frequency can be attributed to a lack of oral hygiene skills. Regarding dental literature to get evidence for the most effective plaque reducing brushing technique, one will not find any evidence. Currently, there is no clear evidence as to which brushing technique would bring about the best oral hygiene skills (Staehle et al., 2007). Randomised controlled studies that compare the different brushing techniques are missing. The aim of the present study is to catch up on this lack of evidence.

**Eligibility criteria**

Participants should be students (except of dentistry), non-smokers, more than 20 own teeth, bleeding and/or plaque on more than 10 sites. Participants should be recruited via postings on the campus and announcements in local magazines.

**Study Design**

After inclusion participants receive in group meetings an instruction in the application of floss to reach a standardized interdental hygiene as far as possible. These skills will be checked several times within the next two weeks. Afterwards all participants receive a professional tooth cleaning and the instruction of one of the three tooth brushing techniques. Dependent variables will be assessed two, six, twelve and twenty-eight weeks after this intervention. All participants receive standardized tooth brushes, toothpaste and floss for the investigation period and they will be encouraged to use these for their daily oral hygiene. After fourteen weeks the materials will be changed and all participants receive new materials. Therefore the participants bring back their old materials.

**Variables that will be observed and determined, respectively**

**Independent variables**

Participants will be stratified by gender and handedness and randomly assigned to one of three groups (Stilman, Fones or Bass).

**Dependent variables**

Dependent variables are oral hygiene skills, actual oral hygiene and oral health. Turesky modification (1970) of plaque index of Quigley and Hein (1962) (TQHI) will be assessed to measure oral hygiene skills and actual oral hygiene. Dental plaque will be stained with Mira-2-Ton solution and to evaluate actual oral hygiene only dark blue stained sites will be evaluate. To measure oral hygiene skills participants will be requested to brush their teeth to the best of their abilities and afterwards the teeth will be stained with Mira-2-Ton solution again and now all staining will be assessed. As an indicator of oral health bleeding will be assessed with the papillary bleeding index by Saxer & Mühlemann modified by Rateitschak (1989).

**Control variables**

All dependent variables will be assessed at baseline. Additionally, periodontitis-related knowledge, dental self-efficacy, pros and cons, stages of change, decisional balance of oral hygiene (for these there are already validated measuring instrument of our working group (Deinzer et al., in preparation; Granrath, 2007; Deinzer et al., 2008)) will be assessed at baseline and 28 weeks after intervention.

**Primary outcome measure**

Primary outcome measure is oral health 28 weeks after intervention.

**Secondary outcome measure**

Secondary outcome measures are oral hygiene skills at 28 weeks and on the other appointments and oral health on the other appointments.

**Potential disturbance variables**

Oral hygiene skills, oral hygiene and oral health parameters could influence the outcome therefore they will be assessed at baseline. Periodontitis-related knowledge, dental self-efficacy, pros and cons, stages of change, decisional balance of oral hygiene will be evaluated with already validated measuring instrument of our working group (Deinzer et al., in preparation; Granrath, 2007; Deinzer et al., 2008) and controlled.

**Biometrical/Statistical Analyses**

Primary outcome measure is oral health 28 weeks after intervention. Secondary outcome measures are oral hygiene skills and oral hygiene at 28 weeks and on the other appointments and oral health on the other appointments. Percentage of unstained sites MPI and TQHI and percentage of sites without bleeding are assessed. The inference-statistical analyses shall be made by [name]. [name].

Statistical data analyses will be conveyed with analysis of variance. Additionally exploratory analyses follow to investigate the effect sizes of group differences.

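### The analysis section names only analysis of variance and does not put baseline bleeding or the stratification factors in the model, so available precision may be forgone

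*Protocol*

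**What the plan says.** The Protocol, under Biometrical/Statistical Analyses, states "Primary outcome measure is oral health 28 weeks after intervention" and measures it as a proportion of sites ("percentage of sites without bleeding are assessed"). The method sentence is "Statistical data analyses will be conveyed with analysis of variance". It covers all outcomes and lists no covariate, baseline term or stratification factor. The only addition is exploratory work on effect sizes.

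Three other sections bear on the model:

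- **Control variables:** "All dependent variables will be assessed at baseline". This includes bleeding, the primary outcome.
- **Potential disturbance variables:** "Oral hygiene skills, oral hygiene and oral health parameters could influence the outcome therefore they will be assessed at baseline". The next sentence lists knowledge, self-efficacy and similar scales and ends "and controlled". As written, that phrase belongs to the psychological scales and not to bleeding.
- **Independent variables:** "Participants will be stratified by gender and handedness and randomly assigned to one of three groups".

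The first amendment replaces the Stillman arm by a control group, so the number of groups remains three.

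**The concern.** The Protocol identifies a likely prognostic variable, measures it and files it under control variables, but the stated analysis does not say that it is used. The two randomisation factors are in the same position. One-way, factorial and repeated-measures analyses of variance all fit the method sentence, and they can give different primary results.

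Two things are at stake if the sentence is followed in its plainest form. Variation between people that baseline bleeding could explain would stay in the error term. A chance baseline difference between groups would also carry into the week-28 comparison, in proportion to the correlation between the two measurements. The trial is sized only for large effects, so groups are probably small and chance differences are not negligible.

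**Working it through.** **Inputs from the Protocol.** Three groups; α = 0.05 and β = 0.20 for large effects (Sample size calculation); continuous primary outcome at 28 weeks, also measured at baseline.

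**Assumptions.** The Protocol text shown gives no sample size, SD, numerical effect, allocation ratio or correlation, so there is no figure to reproduce. I take equal groups, read a large effect as Cohen f = 0.40, and vary the baseline to week-28 correlation ρ from 0 to 0.7.

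**Step 1: reference design.** For a one-way analysis of variance with k = 3 and N = 3n, the noncentrality is λ = N·f², on 2 and N − 3 degrees of freedom. At n = 21 power is 79.8%; at n = 22 it is 81.8%. So 22 per group (N = 66, λ = 66 × 0.16 = 10.56) is the smallest size that reaches 80%.

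**Step 2: baseline adjustment.** Residual variance is multiplied by 1 − ρ², so λ = N·f²/(1 − ρ²), with one error degree of freedom lost. For example, at ρ = 0.5, λ = 10.56/0.75 = 14.08.

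**Step 3: interval width.** The 95% half-width for a pairwise difference, in SD units, is t × √(2/22) × √(1 − ρ²). This is 0.603 without adjustment; the lost degree of freedom is ignored.

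| ρ | Residual variance | Power, f = 0.40 | Half-width (SD) | Narrowing |
|---|---|---|---|---|
| unadjusted | 1.00 | 81.8% | 0.603 | – |
| 0 | 1.00 | 81.8% | 0.603 | 0% |
| 0.2 | 0.96 | 83.4% | 0.590 | 2% |
| 0.3 | 0.91 | 85.4% | 0.575 | 5% |
| 0.5 | 0.75 | 91.7% | 0.522 | 13% |
| 0.7 | 0.51 | 98.4% | 0.430 | 29% |

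**Step 4: other effect sizes.** For a medium effect (f = 0.25, assumed) at the same size, power is 40.9% unadjusted and 44.4, 52.4 and 70.0% at ρ = 0.3, 0.5 and 0.7. If a large effect instead means a pairwise d of 0.80, tested two-sided, 26 per group are needed. Power is then 80.7% unadjusted and 84.2, 90.4 and 97.7% at the same correlations. The pattern does not depend on which definition was meant.

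**Step 5: chance imbalance.** With 22 per group the standard error of a baseline difference between two groups is √(2/22) = 0.30 SD. With equal SDs at both times, an imbalance of that size shifts the unadjusted week-28 difference by about ρ × 0.30 SD: 0.15 SD at ρ = 0.5, and 0.06 SD at ρ = 0.2.

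**Step 6: stratification factors.** If they explain a share R² of the outcome variance, leaving them out overstates the standard error by 1/√(1 − R²) − 1. That is 0 at R² = 0, 2.6% at 5% and 8.5% at 15%. The Protocol gives no R². If the factors explain nothing, including them with baseline (three degrees of freedom in all) changes power by about 0.001 or less.

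**The case against.** The strongest reply is that the Protocol is silent on model terms and does not exclude them. It files baseline values under control variables and potential disturbance variables, and the strata under independent variables, which together suggest that adjustment may be intended. Exact covariates are often left to a statistical analysis plan, which may exist and is not shown.

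Much of this stands. A reader might infer that the Protocol prescribes an unadjusted analysis; it does not say so. It does fix a method by name, though. A continuous baseline score would enter as a covariate, making the method analysis of covariance, which the Protocol does not mention.

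Three further inferences are tempting and unsupported:

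- **That planned power is lost.** If the groups were sized for an unadjusted analysis, the 80% is kept. Only an additional gain is forgone.
- **That omitting the strata inflates the standard errors.** This is so only if gender or handedness predicts bleeding, and the Protocol offers no evidence that either does.
- **That the gain is sure to be substantial.** Everyone receives floss instruction, a professional cleaning and standard materials, and the outcome is read 28 weeks after the intervention. A weak correlation is quite possible, and at 0.2 or below the gain is under two percentage points of power.

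An unadjusted comparison would also be unbiased on average, with a valid type I error rate.

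**Conclusion.** The point holds as a matter of precision and clear specification. It is not an error that would invalidate the result. The stated method does not take up the control variables that the Protocol itself names, and no other section puts baseline bleeding into the model.

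Under the assumed 22 per group and f = 0.40, adjustment gains between nothing (ρ = 0) and about 17 percentage points of power (ρ = 0.7), with about 10 points at ρ = 0.5. The size rests on a correlation the Protocol does not supply. The recommendation does not, because the cost is close to zero even if the correlation is nil. The case for the strata is weaker: including them matches the analysis to the randomisation at almost no cost, but any gain depends on their being prognostic.

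**What to change.** In Biometrical/Statistical Analyses, replace the method sentence by wording such as: the 28-week percentage of non-bleeding sites will be compared between groups by analysis of covariance, with group as factor, the baseline percentage of non-bleeding sites as covariate, and gender and handedness as further factors. Specify the same model for oral hygiene skills, with the baseline skills score as covariate. Report adjusted mean differences with 95% confidence intervals. If a statistical analysis plan already contains this model, a cross-reference to it is enough.

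The cost is a sentence or two of text and about three degrees of freedom. No new data, visits or participants are needed.

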**Sample size calculation**

Group size was determined to allow for the detection of large effect sizes with an α-error probability of p≤ 0.05 and a β-error probability of p≤ 0.20.

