**List of Amendments**

1.) Presentations of the Stillman technique turned out to be very similar to those of the Bass technique. Indeed, pictures and videos of the two techniques were hardly to differentiate. We thus decided to omit the Stillman technique and to inculde a control group instead, which was taught only basics of tooth brushing and no specific brushing technique.

2.) Data on oral hygiene (dark blue staining prior to tooth brushing) were excluded from analyses due to a misunderstanding when assessing oral hygiene. While maufacturer proposes to assess all blue staining in order to assess older deposits we assessed dark blue staining, only. Since gingivitis is considered another good clinical indicator for oral hygiene we focused this parameter instead.

3.) Data of the two-week-assessment point were omitted from analyses as this point in time turned out to be too close to the professional tooth cleaning with nearly no bleeding and very low degree of staining after tooth brushing (indeed, the loweset observed in all groups throughout the study) both obviously reflecting the favorable after-effects of the professional tooth cleaning rather than oral hygiene activities of the participants.

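### The only confirmatory method named, analysis of variance, leaves out participants without a week-28 score unless values are imputed, although their earlier bleeding scores are in hand

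*Protocol*

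**What the plan says.** The protocol's section on biometrical and statistical analyses gives the method in one sentence: "Statistical data analyses will be conveyed with analysis of variance". The only addition is exploratory work on effect sizes. The section does not say whether the ANOVA is one-way, covariate-adjusted or repeated-measures.

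The primary endpoint is a single time point: "Primary outcome measure is oral health 28 weeks after intervention". Bleeding is analysed as a percentage of sites ("percentage of sites without bleeding are assessed").

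The same measure is taken repeatedly. Under Study Design, "Dependent variables will be assessed two, six, twelve and twenty-eight weeks after this intervention". Under Control variables, "All dependent variables will be assessed at baseline". Amendment 3 then takes one visit out of the analysis: "Data of the two-week-assessment point were omitted from analyses as this point in time turned out to be too close to the professional tooth cleaning". The scores now available for analysis are therefore baseline and weeks 6, 12 and 28. None of the three amendments changes the method.

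The sample size section aims at "detection of large effect sizes with an α-error probability of p≤ 0.05 and a β-error probability of p≤ 0.20", without a numerical effect size or a number per group.

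**The concern.** In its usual form, ANOVA uses complete records. Applied at week 28, it needs a week-28 value. In repeated-measures form, it needs every included visit. A student who attends weeks 6 and 12 and then leaves would add nothing to the primary comparison unless a value is imputed. The interval from week 12 to week 28 is the longest without a scheduled assessment, so this pattern of loss is plausible.

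Two things are at stake. The first is power: each participant left out reduces the number behind the week-28 test. The second, and more important, is bias. If leaving is related to how much a participant was bleeding at earlier visits, and differs between arms, the participants who remain are no longer comparable. The earlier scores that could correct for this are collected, but the named method does not use them for this purpose.

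**Working it through.** The protocol text at hand gives no group size, dropout rate or numerical effect, so there is no stated figure to reproduce. What follows is an illustration.

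**Inputs from the protocol:** three groups; alpha 0.05; beta at most 0.20; week-28 endpoint; analysed visits 6, 12 and 28.

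**Assumptions:** a large effect means f = 0.40; equal allocation; loss of 5% to 30%; correlations between visits as given below.

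**1. Reference size.** One-way ANOVA, noncentral F with 2 and N − 3 degrees of freedom and noncentrality N·f² = 0.16·N. The smallest equal group size with power of at least 80% is 22 per arm: N = 66, noncentrality 10.56, power 81.8%. With 21 per arm, power is 79.8%.

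**2. Power when only those with a week-28 score are analysed.** The same formula with N = 66·(1 − loss):

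| Loss | N analysed | Power |
|---|---|---|
| 0% | 66 | 81.8% |
| 5% | 62.7 | 79.6% |
| 10% | 59.4 | 77.1% |
| 15% | 56.1 | 74.4% |
| 20% | 52.8 | 71.5% |
| 30% | 46.2 | 64.8% |

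The first losses are absorbed: power is 81.2% at N = 65 and 80.5% at N = 64. It first falls below 80% at N = 63 (79.8%), that is, after three losses.

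**3. Repeated-measures ANOVA.** If each analysed visit is missed independently with probability 5%, the share of participants removed is 1 − 0.95³ = 14.3%. At 10% per visit it is 1 − 0.90³ = 27.1%. For week 28 alone the shares are 5% and 10%.

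**4. Bias.** Suppose 20% of one arm is lost, all drawn from those with above-median bleeding at the previous visit. For a standard normal score, the mean above the median is 0.798. The remaining 80% then have an earlier-visit mean shifted by 0.2 × 0.798 / 0.8 = 0.20 SD. Multiplying by the correlation with week 28 gives the week-28 bias:
- correlation 0.4: 0.20 × 0.4 = 0.08 SD
- correlation 0.6: 0.12 SD
- correlation 0.8: 0.16 SD

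The arm looks better than it is. A harsher simulated case, in which one arm loses exactly its worst 20% on the earlier score, gives 0.10, 0.17 and 0.24 SD for correlations of 0.3, 0.5 and 0.7. Once the earlier score is modelled, the simulated bias falls to about 0.

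**5. Power regained by using the earlier scores (20% loss).** Two approximations:
- One earlier score with correlation ρ to week 28: effective N = 52.8 + 13.2·ρ². For ρ = 0.3, 0.5 and 0.7 this is 54.0, 56.1 and 59.3, with power 72.6%, 74.4% and 77.0%. The gain over 71.5% is about 1 to 5.5 points.
- Weeks 6 and 12 together, all correlations 0.6: R² = 2 × 0.36 / 1.6 = 0.45. Effective N = 66 / (0.55/0.8 + 0.45) = 66 / 1.1375 = 58.0, with power about 76%.

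Neither restores 80%. At 10% loss the one-score approximation gives 77.6% to 79.5%, a gain of about 0.5 to 2.4 points.

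**The case against.** The strongest objection is that leaving these participants out is a default of the method and not something the protocol lays down. A reader might infer that the protocol commits the trial to a completers' analysis. The text does not support that: it neither prescribes complete cases nor rules out imputation, and ANOVA can be run on imputed data. The form of the model, the analysis set and the handling of missing values may also be set out in an analysis plan that is not shown, and their absence here is not a fault. This stands, and it is why the point is conditional on no imputation. It does not remove the point, because the method itself is stated. An analysis plan that used a mixed model would depart from what the protocol names.

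Two other stronger readings also fail:
- A reader might count four follow-up visits and conclude that missing any of them removes a person. Amendment 3 takes week 2 out, so a participant who misses only week 2 loses nothing, and the three-visit figure of 14.3% applies.
- A reader might infer that the power target is missed as soon as anyone is lost. Even on the assumed 22 per arm it takes three losses. The real group size may include an allowance for dropout, so a shortfall cannot be shown from the protocol.

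It is also fair to say that the bias example is constructed. Loss of the same kind and amount in every arm would largely cancel in the comparison.

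**Conclusion.** The point holds as a weakness in the stated method for the primary analysis. For an endpoint measured repeatedly, the protocol names only a method that, without imputation, leaves out participants whose baseline and earlier scores are available.

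How much this matters cannot be established from the document. On the assumptions above, power would be about 77% at 10% loss and 71.5% at 20%, and selective loss in one arm would bias that arm by 0.08 to 0.16 SD. The effect size, group size, loss and correlations are all assumed. The gain in power from changing the method is modest. The case for the change rests mainly on protection from bias when loss depends on observed earlier bleeding. It is a worthwhile and cheap improvement, and does not imply that the trial is invalid.

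**What to change.** In the section on biometrical and statistical analyses, replace analysis of variance for the primary outcome with a linear mixed model for repeated measures:
- **Outcome:** percentage of sites without bleeding at weeks 6, 12 and 28.
- **Effects:** arm, visit, arm-by-visit and baseline bleeding, which is already collected.
- **Covariance and inference:** a prespecified within-person covariance and small-sample degrees of freedom, for example Kenward-Roger.
- **Participants:** everyone randomised with at least one of these three visits, analysed in the arm to which they were assigned.
- **Primary test:** the comparison of arms at week 28 from this model.

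Use the same model for oral hygiene skills.

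The change costs some wording and a standard software routine, with no new data or visits. There are two downsides. The covariance structure must be fixed in advance, and the result is valid only if missingness depends on observed scores (missing at random). It would not correct for loss driven by unobserved week-28 bleeding.
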